## Abstract

**Introduction:** Rehabilitation approaches have been used for people with stroke to decrease spasticity and improve functions, but little is known about the effect of neuromuscular electrical stimulation (NMES) in this population. Therefore, the primary purpose of this study was to establish a protocol for a double-blinded randomized clinical trial to examine using NMES on plantarflexors spasticity, dorsiflexor muscle strength, physical functions, and self-reported health outcomes in people with chronic stroke in Saudi Arabia.

**Material and Methods:** This randomized clinical trial with two arms and double-blinded registered in ClinicalTrials (NCT04673045) will enroll 44 participants with chronic stroke and randomized them into either the experimental group (EG), including electrical stimulation (ES) with conventional therapy or the control sham group (NMES_sham_) including placebo electrical stimulation with conventional therapy. The frequency will be set at 80 Hz for 30 min. The intervention will be three times a week for 4 weeks for both groups. Data collection for pre- and post-intervention outcomes will include measurements for the primary outcomes including paretic limb (plantarflexor spasticity, ankle range of motion, and dorsiflexor muscles strength), and gait speed using 10-m walk test (10-MWT). The secondary outcomes including mobility function using Timed Up and Go (TUG), walking endurance using 6 Minutes Walk Test (6-MWT), activity of daily living using the Arabic version of Barthel Index (BI), and self-reported health measures such as quality of life using the Medical Outcomes Survey (Short Form 36, SF-36), physical activity using Rapid Assessment of Physical Activity (RAPA), depression symptoms using Patient Health Questionnaire-9 (PHQ-9), fatigue level using Fatigue Severity Scale (FSS), and risk of fall using Fall Efficacy Scale International (FES-I). An independent *t*-test will be utilized to examine the effect of the intervention on the outcome measures.

**Results:** The recruitment has started and is ongoing.

**Conclusions:** Using 4 weeks of NMES will provide information about its effect in improving plantarflexor spasticity, dorsiflexor muscles strength, gait speed, mobility functions, and other self-reported health outcomes in people with chronic stroke when compared to NMES_sham_.

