### Study Design

This study is a two-arm, parallel, double-blinded, single-site, randomized clinical trial (RCT) with two independent variables, between-subject factor (group), and within-subject factor (time). The independent variable of groups has two levels: active NMES (experimental group) and placebo group. The independent variable of time has two levels: baseline (T_0_) and post-intervention (T_1_). The participants will be assigned randomly on a 1:1 ratio into either the experimental group (EG) or to the placebo group (NMES_sham_). Outcomes assessor and participants are blinded to the allocation of groups.

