### Outcome Measures

Primary and secondary outcome measures will be collected by a blinded trained assessor at the baseline and after the intervention (4 weeks of intervention). Primary outcomes will include spasticity in the plantarflexor muscles in paretic leg measured by MAS, active and passive ROM for the ankle joint in paretic leg measured by a handheld goniometer, muscle strength for the ankle dorsiflexor muscle in paretic leg measured by manual muscle testing (MMT), gait speed using 10-meter walk test (10-MWT). Secondary outcome measures will include mobility function using Timed Up and Go (TUG), walking endurance using 6 MWT, ADL using the Arabic version Barthel index (BI), and self-reported health measures such as Medical Outcomes Survey (Short Form-36, SF-36), physical activity using RAPA, depression symptoms using Patient Health Questionnaire-9 (PHQ-9), fatigue level using the Arabic version of Fatigue Severity Scale (FSS), and risk of fall using the Arabic version of Fall Efficacy Scale International (FES-I).

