##### 10-Meter Walk Test

The 10-MWT assesses self-selected preferred walking speed over a short duration with or without an assistive device. The participant will be asked to walk a total of 10 m where an acceleration zone is used for the participants to accelerate 2 m before entering the 6-m distance and 2 m to decelerate afterward. Speed is only calculated for the 6-m distance between the end zones. The 10-MWT is widely used in clinical practice and research for people with stroke and has been shown to have an excellent test–retest reliability (ICC > 0.95) (15). The minimal clinically important difference (MCID) is 0.14 m/s for substantial meaningful change (16). The test will be performed three times, and the resulting speeds obtained will be averaged and used for the analysis. The test will be performed at the baseline and post-intervention.

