### Statistical Analysis

IBM SPSS Version 25.0 (IBM Corp., Armonk, NY, USA) will be used to analyze the collected variables. The descriptive demographic information (means, medians, and SD) include age, gender, onset of the stroke, height, weight, and all outcome measures will be calculated and compared at the baseline using the independent *t*-test or chi-square test to ensure that there is no significant difference between the two groups at the baseline. Normality of the data will be assessed using the Shapiro–Wilk test. Comparisons between pre- and post-intervention will be conducted using the dependent *t*-test or the Wilcoxon signed rank test to determine if there will be significant differences between two different timepoints for each group. The independent *t*-test or the Mann–Whitney *U*-test will be used to compare the recorded values at the post-intervention between the two groups. In case of confounding variables such as age, secondary analysis will be performed according to the age groups (18–30, 31–50, and 51–65 years). In order to account for pre- and post-intervention between-group clinical effectiveness in terms of the outcome measures, Cohen's *d* effect size will be calculated. Furthermore, the pre-test effect sizes will be subtracted from the post-test effect sizes to effectively control for the differences at the baseline and obtain the absolute effect size. Effect sizes will be defined as small (*d* ≤ 0.2), medium (0.2 > *d* < 0.8), and large (*d* ≥ 0.8) (43). Differences will be considered statistically significant when *p* < 0.05.

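### The only between-group significance test leaves out the baseline measured on every outcome, which costs precision and lets the p-value disagree with the plan's own baseline-corrected effect size

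*Protocol article*

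**What the plan says.** All places are in the protocol article.

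- **Statistical Analysis, between groups.** An independent t-test or Mann-Whitney U-test "will be used to compare the recorded values at the post-intervention between the two groups". The Abstract names the independent t-test as what "will be utilized to examine the effect of the intervention on the outcome measures".
- **Outcome Measures.** "Primary and secondary outcome measures will be collected by a blinded trained assessor at the baseline and after the intervention". A baseline therefore exists for every outcome.
- **Study Design.** The trial is described "with two independent variables, between-subject factor (group), and within-subject factor (time"), each factor with two levels. No group-by-time term appears in the Statistical Analysis section.
- **Statistical Analysis, other uses of baseline.** Paired tests are run "to determine if there will be significant differences between two different timepoints for each group". Baseline values are compared "to ensure that there is no significant difference between the two groups at the baseline". For the effect size, "the pre-test effect sizes will be subtracted from the post-test effect sizes to effectively control for the differences at the baseline". The age-group analysis in the same section concerns age, not the outcome's own baseline.

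**The concern.** This is a test the article states, not a detail left to an analysis plan. It does not analyse the group-by-time design that the article describes.

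Two consequences follow. First, variation between patients that the baseline value could explain stays in the error term, in a trial of 44. Second, a chance baseline difference passes in part into the post-intervention contrast. The planned safeguard is a significance test at baseline, which at this size cannot detect a gap large enough to matter.

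The plan itself recognises the need to correct for baseline, but does so only in an effect size without an interval. If the p-value and that effect size point different ways, the article gives no rule for which one answers the question.

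**Working it through.** **Inputs from the article.** 44 patients, 22 per arm, 10% attrition (Sample Size Calculation); significance at p < 0.05, taken as two-sided (Statistical Analysis); 0.14 m/s cited as an important change in gait speed (10-Meter Walk Test). Evaluable: 44 × 0.9 = 39.6, about 20 per arm.

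**Assumptions.** The article gives neither the gait-speed SD nor the pre-post correlation r. I take SD = 0.25 m/s (range 0.20 to 0.30) and r from 0.3 to 0.8. The trial's own power cannot be reproduced, because no effect size, SD or target power is stated.

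**1. Precision.** The post-only t-test has standardised difference d = 0.14/0.25 = 0.56, with noncentrality d√(n/2) = 0.56 × √10 = 1.77 on 38 df. ANCOVA reduces the residual variance by the factor 1 − r², so d becomes 0.56/√(1 − r²) on 37 df. The last column is 40/(1 − r²), the number the post-only test would need to match ANCOVA on 40 patients.

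| Analysis | 1 − r² | effective d | power | matching post-only N |
|---|---|---|---|---|
| Post-only | 1 | 0.56 | 41% | 40 |
| ANCOVA, r = 0.3 | 0.91 | 0.59 | 44% | 44 |
| ANCOVA, r = 0.5 | 0.75 | 0.65 | 51% | 53 |
| ANCOVA, r = 0.7 | 0.51 | 0.78 | 68% | 78 |
| ANCOVA, r = 0.8 | 0.36 | 0.93 | 82% | 111 |

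At SD 0.20 and 0.30, post-only power is 58% and 30%. With adjustment it is 62% and 33% at r = 0.3, and 95% and 67% at r = 0.8.

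**2. What the baseline test lets through.** The largest non-significant standardised gap is t(0.975) × √(2/n). At 22 per arm this is 2.018 × 0.3015 = 0.61 SD; at 20 per arm, 2.024 × 0.3162 = 0.64 SD. By chance alone, a gap above 0.5 SD has probability about 10% at 22 per arm and 11% at 20 per arm.

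**3. How much carries over.** With equal SDs at both times, a baseline gap b shifts the expected post-only contrast by r × b. For b = 0.5 SD this is 0.25 SD at r = 0.5 and 0.40 SD at r = 0.8.

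Given that gap and no treatment effect, at 20 per arm the post-only contrast has mean 0.5r and SD √(1 − r²) × 0.316. Its significance limit is 1.96 × 0.316 = 0.62.
- r = 0.5: (0.62 − 0.25)/0.274 = 1.35, so the conditional false-positive rate is about 9%.
- r = 0.8: (0.62 − 0.40)/0.190 = 1.16, about 12%.

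Using the t critical value 2.024 instead of 1.96 gives about 8% and 10%. These rates are conditional on the gap. Averaged over all randomisations the rate is 5%.

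**4. Disagreement between p-value and effect size.** At 20 per arm the post-only test is significant once d exceeds 0.64. Take a post-test d of 0.65 and a pre-test d of 0.50 in the same direction. The baseline test is non-significant (0.50 < 0.61), and the post-only test is significant (0.65 × √10 = 2.06 > 2.024). The planned corrected effect size is 0.65 − 0.50 = 0.15, which the plan's own scale calls small.

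**5. The subtraction as a correction.** With similar SDs, post d minus pre d is a standardised difference in change. The variance of a change relative to a post value is 2(1 − r): 1.4 at r = 0.3, 1.0 at r = 0.5, 0.4 at r = 0.8. ANCOVA's 0.91, 0.75 and 0.36 are lower each time, and below r = 0.5 the subtraction is noisier than no correction.

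**The case against.** **The plan does not ignore baseline.** This stands. A reader who stops at the t-test might infer that baseline plays no part between groups. The same section subtracts pre-test from post-test Cohen's d, which is close to the group-by-time contrast. What remains is that this figure has no test or interval described, while the p-value is uncorrected.

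**The post-only test is valid.** This also stands. A reader might infer bias or an inflated error rate. Under the planned 1:1 random allocation the comparison is unbiased and its unconditional type I error is 5%. The 8% to 12% above applies only once a 0.5 SD gap has occurred.

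**The gain may be small.** This stands in part. It is tempting to take the article's "excellent test–retest reliability (ICC > 0.95") for the 10-metre walk as proof that baseline explains most of the post-treatment variance. That figure is test-retest reliability, not the correlation across 4 weeks of rehabilitation, and it concerns one outcome. At r = 0.3 the gain is only 2 to 4 points. A low correlation is plausible for MAS, because entry is restricted to grade 2 or above, and for the coarse muscle-strength grades. Still, adjustment did not lose power at any correlation examined.

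**0.14 m/s is not the design effect.** Correct. The article cites it as a substantial meaningful change and does not size the trial on it, so the power figures illustrate a mechanism and are not this trial's power.

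**Conclusion.** The point holds in a limited form. The sole between-group significance test omits the baseline. The only baseline correction is an effect size without described uncertainty, so the two can conflict and nothing says which governs.

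For gait speed under the stated assumptions, the post-only test gives up about 3 points of power at r = 0.3, about 10 at r = 0.5 and about 41 at r = 0.8. The SD and the correlation are not in the article, so a flat statement that the trial loses much of its power is not supported. No figure is offered for MAS or muscle strength, because the article gives no grade distribution from which to derive one.

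The imbalance thresholds (0.61 SD at 22 per arm, 0.64 at 20) need only the arm size and the significance level. The 0.25 to 0.40 SD carry-over also needs the assumed correlation. This is an improvement available at no data cost, not a failure of validity.

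**What to change.** - **Continuous outcomes and multi-item scores** (range of motion, gait speed, TUG, 6-minute walk, Barthel Index, SF-36, PHQ-9, FSS, FES-I): make the primary between-group analysis an ANCOVA of the T1 value on group and the T0 value of the same outcome. Report the adjusted difference with its 95% CI.
- **Ordinal outcomes** (MAS as six ordered grades, MMT, RAPA levels): use rank ANCOVA with the baseline grade as covariate. With about 20 per arm and baseline MAS confined to grades 2 to 4, sparse grades make a proportional-odds model fragile.
- **Effect size:** let the adjusted analysis replace the pre/post Cohen's d subtraction, so that there is one baseline correction and not two.
- **Baseline table:** keep it descriptive, and stop using its significance test as the safeguard.
- **Post-only t-test or Mann-Whitney:** keep as a sensitivity analysis.

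The cost is one paragraph and one degree of freedom per outcome, with no new data. The Abstract reports recruitment as ongoing, so the change should be made and dated before outcome data are analysed.

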##### Fatigue Severity Scale

It is a self-reported questionnaire that consists of **nine** statements that rate the severity of the fatigue interference of the patient with certain activities. The items are scored from 1 to 7 with 1 = strongly disagree and 7 = strongly agree. The minimum score = 9 and the maximum score possible = 63. The higher score indicates greater fatigue severity (32). The mean score of the **nine** items will be used for statistical analysis. The FSS has been shown to have high internal consistency, good test–retest reliability, and good concurrent validity in several populations (33–35). The FSS scale has been translated and validated into the Arabic language (36).

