## Discussion

The main objective of this clinical trial is to evaluate the effect of using NMES on plantarflexor muscle spasticity, ankle ROM, dorsiflexor muscle strength, and gait speed. The secondary objective of this work is to examine the effect of using NMES on mobility function, walking endurance, and self-reported outcomes such as ADL, QoL, physical activity, depression symptoms, fatigue level, and risk of fall.

The findings from this study will highlight the importance and effect of using electrical stimulation during a rehabilitation program for individuals with chronic stroke living in Saudi Arabia. If the findings are positive, this study will be the first that has preliminary positive results for a rehabilitation program using NMES in this population in Saudi Arabia. The results will eventually help healthcare providers and other researchers in choosing and investigating the appropriate rehabilitation approach to improve spasticity and functionality.

Upon completion of data collection, it is expected that the active NMES group will benefit from decreased ankle plantarflexors spasticity, increased dorsiflexors strength, and improved walking function, physical activity, and QoL. The placebo group will gain benefit from CRP; however, it is expected that the scores of placebo group in targeted outcomes will show less variation than EG. The result will be published after the data and the study is completed.

Although this study has some strengths including blinded assessors, blinded participants, and placebo NMES to decrease bias, there are some limitations. A single center study is a possible limitation that may limit the generalizability of the results. Using a clinical setting (hospital outpatient clinic) with lack of tools is another limitation that may limit the use of objective tools such as EMG. Drop out is another limitation that may occur in clinical trials that affects sample size and results. Lack of follow-up assessment after the intervention is another limitation due to limited financial resources that affect the results of long-term effect and persistence of the results of this treatment.

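### The effect-size rule is wrong as written: the medium band is mis-written, the bands have no stated direction, and subtracting pre-test d over-corrects a chance baseline imbalance

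*Protocol article*

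**What the plan says.** All of this is in the Statistical Analysis section of the protocol article.

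- To express clinical effectiveness between groups, "Cohen's *d* effect size will be calculated" for the pre- and post-intervention data.
- Baseline is handled by a difference of two effect sizes: "the pre-test effect sizes will be subtracted from the post-test effect sizes to effectively control for the differences at the baseline". The stated purpose is to "obtain the absolute effect size".
- The result is graded: "Effect sizes will be defined as small (*d* ≤ 0.2), medium (0.2 > *d* < 0.8), and large (*d* ≥ 0.8").
- The between-group test uses follow-up values only: the t-test or Mann–Whitney test "will be used to compare the recorded values at the post-intervention between the two groups". The significance rule is "Differences will be considered statistically significant when *p* < 0.05".

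The section does not say which group is subtracted from which, or whether the bands apply to d or to its modulus. The direction of benefit differs between outcomes. The Discussion says that "it is expected that the active NMES group will benefit from decreased ankle plantarflexors spasticity, increased dorsiflexors strength", so a good result is a lower MAS grade and a higher MMT grade. For the Fatigue Severity Scale, "The higher score indicates greater fatigue severity".

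**The concern.** The rule has three parts, and each has a fault as written.

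1. The middle band has its first inequality sign the wrong way round.
2. The bands are on d, with no direction stated. If d is active minus sham, benefit on MAS, TUG, PHQ-9, FSS and FES-I is negative, and every negative number is below 0.2.
3. A difference of two standardised differences is said to control effectively for baseline. It does so fully only if a baseline gap persists one-for-one to follow-up.

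The main comparison uses post-intervention values alone, so this subtraction is the only adjustment for baseline outcome values that the section states. It also supplies the trial's measure of clinical effectiveness. With 22 per arm, chance imbalances of a few tenths of an SD are ordinary. At stake are the size and the label of the reported effect.

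**Working it through.** **Inputs.** Bands, subtraction rule and post-only test: Statistical Analysis. Sample: 22 per arm with 10% attrition (Sample Size Calculation), so 44 × 0.9 = 39.6, or about 20 completers per arm. The pre-post correlation ρ and the ratio of post to pre SD are not given; I take ρ from 0.3 to 0.9 and SD ratios from 0.8 to 1.5 as assumptions.

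**Step 1: the bands as printed.** The medium band requires d < 0.2 and d < 0.8 together, which is just d < 0.2.

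| d | Label as printed | Label with bands on the modulus, sign corrected |
|---|---|---|
| −1.2 | small and medium | large |
| −0.5 | small and medium | medium |
| 0.1 | small and medium | small |
| 0.2 | small | small |
| 0.3, 0.5, 0.79 | none | medium |
| 0.8, 1.2 | large | large |

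**Step 2: direction.** The negative rows show what follows if d is active minus sham and keeps its sign: a benefit of 1.2 SD on a lower-is-better outcome is never called large. Correcting the inequality sign does not cure this, because −1.2 still satisfies d ≤ 0.2.

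**Step 3: the subtraction.** With equal SDs, true effect δ and observed imbalance d_pre, approximately:

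- E[d_post | d_pre] = δ + ρ·d_pre
- E[d_post − d_pre | d_pre] = δ − (1 − ρ)·d_pre

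The error is zero only when ρ = 1. Otherwise the arm that started worse is credited with benefit. The typical size of d_pre is its standard error, √(2/22) = 0.30, so a one-SE imbalance contributes 0.7 × 0.30 = 0.21, 0.5 × 0.30 = 0.15, 0.3 × 0.30 = 0.09 and 0.1 × 0.30 = 0.03 at ρ = 0.3, 0.5, 0.7 and 0.9.

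Simulation (40,000 trials per setting, 20 per arm, equal SDs) agrees. The last three columns are mean estimates when the true effect is 0.5 and d_pre is about 0.4 (between 0.3 and 0.5):

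| ρ | Slope of d_post − d_pre on d_pre | d_post alone | d_post − d_pre | ANCOVA |
|---|---|---|---|---|
| 0.3 | −0.71 | 0.63 | 0.24 | 0.50 |
| 0.5 | −0.51 | 0.71 | 0.32 | 0.50 |
| 0.7 | −0.31 | 0.78 | 0.39 | 0.49 |
| 0.9 | −0.10 | 0.86 | 0.48 | 0.50 |

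The ANCOVA slope on d_pre is about 0 throughout. Averaged over all randomisations, the subtraction gives about 0.51 for a true 0.50, so there is no material bias on average.

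**Step 4: precision.** Large-sample standard errors with n = 20 per arm:

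- post only: √(2/n) = 0.316
- subtraction: √((2/n)·2(1 − ρ)) = 0.374, 0.316, 0.245, 0.141 at ρ = 0.3, 0.5, 0.7, 0.9
- ANCOVA: √((2/n)(1 − ρ²)) = 0.302, 0.274, 0.226, 0.138

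Under no effect, with SDs estimated from the data, the simulated SDs of subtraction against ANCOVA are 0.39 v 0.32, 0.33 v 0.28 and 0.26 v 0.24 at ρ = 0.3, 0.5 and 0.7. ANCOVA is more precise at every ρ tested. Below ρ = 0.5 the subtraction is less precise than no adjustment.

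**Step 5: two different SDs.** d_pre and d_post are each divided by their own SD. If a raw gap of 0.4 baseline SD stays exactly the same, the subtraction returns 0.4/0.8 − 0.4 = +0.10 when the post SD is 0.8 of baseline, and 0.4/1.5 − 0.4 = −0.13 when it is 1.5 times baseline. For MAS, unequal spread is plausible: the Inclusion Criteria require a grade of at least 2, so baseline can take only grades 2, 3 and 4, while follow-up can take all six grades.

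**The case against.** The case on the other side has real weight.

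- **The band is a slip, not an impossibility.** A reader might infer that no value can satisfy the printed inequality. That is not so: every d below 0.2 satisfies it. The neighbouring bands point to one sensible reading, 0.2 < d < 0.8. What stands is that the printed text must be corrected.
- **The sign fault is conditional.** A reader might infer that large benefits will be labelled small. The article fixes no sign convention, the Discussion gives the expected direction of benefit, and the word absolute may mean a modulus. The modulus reading does not settle the rule, however. Taken before subtraction, a swing from −0.3 to +0.3 scores zero; taken after, benefit and harm look alike. A stated convention is still needed.
- **The subtraction is not worthless.** A reader might infer that it is biased or does nothing about baseline. With equal SDs it is a standardised change-score contrast, unbiased on average under randomisation. Above ρ = 0.5 it depends less on baseline than d_post alone and is more precise. What stands is that the claim of effective control fails for a chance imbalance unless ρ is near 1, and that ANCOVA does better from the same data.
- **Inference is untouched.** The p < 0.05 tests do not use these effect sizes, and the article gives separate change benchmarks for gait speed, TUG and the Barthel Index. This limits the severity.

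Two further complaints would go too far. Preferring other cut-points than 0.2 and 0.8 is a choice among conventions. The absence of a stated confidence interval is a detail that an article may leave to the full plan.

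**Conclusion.** The point holds as a moderate issue in three parts.

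1. The medium band is mis-written. This needs no assumption.
2. The bands lack a direction. Mislabelling follows if d is taken as active minus sham and keeps its sign.
3. The subtraction over-corrects a chance imbalance by (1 − ρ) × d_pre. For a one-SE imbalance this runs from about 0.21 at ρ = 0.3 to 0.03 at ρ = 0.9. It costs precision against ANCOVA, clearly at low ρ and little at high ρ.

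The figures in part 3 rest on normal outcomes, equal SDs and an assumed ρ; unequal SDs add a separate distortion of about 0.1 in the examples shown. The documents do not support a stronger conclusion that the trial's significance tests are wrong or that the estimate is biased over repeated randomisation.

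**What to change.** In the Statistical Analysis section, before outcome data are analysed:

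1. Correct the medium band to 0.2 < |d| < 0.8, apply all three bands to |d|, and report the direction of benefit separately. Alternatively, orient d so that positive means benefit on every outcome.
2. For continuous outcomes, replace the subtraction with the group difference at follow-up adjusted for the baseline value (ANCOVA), divided by the pooled baseline SD.
3. For MAS and MMT, which are ordinal primary outcomes, do not use the subtracted d. Use a rank-based or ordinal-model effect measure adjusted for baseline grade.
4. Remove the claim that the subtraction effectively controls for baseline differences.

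The cost is a few sentences and no extra data, since every outcome is already measured at baseline. The change does add models that the section does not now contain. It should therefore say that they supply the effect sizes and how they are to be read beside the post-only tests.
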